Given the limitations of face-to-face approaches, such as restricted accessibility, there has been growing interest in delivering preventive approaches through digital platforms. Evidence for digital interventions reveals both substantial promise and important limitations. Internet- and mobile-based interventions (IMIs) can reduce depressive and anxiety symptom severity (6, 8, 9) and the relative incidence of MDD in adults by 28% within a year (10), while mental health apps demonstrate overall small but significant effects on symptoms of depression and anxiety (11, 12). Research indicates that specific app features, such as CBT components, mood monitoring, and chatbot technology, are associated with larger effect sizes (12). In addition, substantial empirical evidence now supports CBT-based digital interventions as effective low-intensity interventions for subclinical symptom management and as resource-efficient, accessible tools for targeted prevention programs (13). However, similar to face-to-face approaches, preventive digital interventions do not benefit all users equally, and a notable proportion of participants still develop full-blown disorders despite intervention (10). When interventions fail to meet individual needs, this can result in high dropout rates, low adherence and engagement, and reduced effectiveness (14, 15)—an issue particularly pronounced in mental health related mobile interventions (16).

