##### Randomization

3.2.1.3

Eligible individuals will be randomly allocated to the IG or WLC by an independent researcher using block randomization (blocks of 4 and 6 to minimize predictability in allocation) via Sealed Envelope.^1^ Participants will be informed of their group allocation; those in the IG will receive immediate access to the CaYou app, while WLC participants will gain access after 4 weeks.

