#### Sample size and power calculation

3.2.3

For stage II, the sample size was calculated following pilot study guidelines (69). To detect a very small effect (*d* < 0.3) on the PHQ-4 at post-assessment (*α* = 0.05, *β* = 80%), and accounting for an anticipated 20% dropout rate, *n* = 30 participants per group are required, yielding a total sample size of *N* = 60 participants.

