
**Table 3 tab3:** Traffic light system for assessing feasibility.

Traffic light system for assessing feasibility	Green	Yellow	Red
1. Participants recruited during the planned period (%)	*N* = 60 (100%)	*N* = 45–59 (75–98%)	*N* < 45 (<75%)
2. Participants with complete data at post-assessment (percentage of the total sample)	>70%	50–70%	<50%
3. Completed EMA data (at least one EMA completed per day; percentage of the total sample)	>60%	40–60%	<40%
4. Omega value for two-thirds of the outcome questionnaires	≥0.70	0.60–0.69	<0.59
5. Satisfaction (ZUF-8)	*M* > 26	*M* = 24–26	*M* < 24
6. Pre-post change in the PHQ-4 scores compared to the control group (depression and anxiety subscales)	Baseline score ≤3: No reliable deterioration, indeterminate, or reliable improvement Baseline score > 3: No deterioration or improvement reliable to deterioration and improvement	No improvement reliable to improvement in participants with a baseline score > 3	Symptom deterioration reliable to deterioration
7. Risk–benefit ratio	Positive	Negative: Isolated negative intervention-related events, that can be addressed by revising the intervention or study	Negative: Serious adverse intervention-related events (e.g., suicidal thoughts), symptom deterioration

EMA, Ecological Momentary Assessment; ZUF-8, Questionnaire for Patient Satisfaction 8.

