##### Quantitative data analysis

3.2.5.1

The intervention is considered feasible if all criteria in the traffic light system are rated yellow or green (see Table 3). Yellow ratings will prompt internal discussion and minor adjustments; red ratings indicate the need for major revisions, with input from external experts. Quantitative baseline data will be analyzed descriptively. Mental health outcomes will be examined using analysis of covariance (ANCOVA) to assess between-group pre-post changes, and time series analyses will explore individual symptom trajectories based on 4-day intervals.

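### Criterion 2 in Table 3 rates post-assessment completeness on both arms pooled, so good waitlist retention can mask heavy loss in the intervention group on that row

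*Protocol article*

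**What the plan says.** Table 3 (Feasibility measures) lists seven traffic-light criteria. Criterion 2 is "Participants with complete data at post-assessment (percentage of the total sample"), with cut-offs of more than 70% (green), 50–70% (yellow) and less than 50% (red). The denominator is stated outright, so it is not a detail left to another document.

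Under Quantitative data analysis the decision rule reads: "The intervention is considered feasible if all criteria in the traffic light system are rated yellow or green". A yellow rating leads to internal discussion and minor adjustments, a red one to major revision.

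Under Sample size and power calculation, "n* = 30 participants per group are required, yielding a total sample size of *N* = 60 participants", after "accounting for an anticipated 20% dropout rate". That dropout figure is not split by arm. Under Randomization the waitlist group gets the app only after 4 weeks. Under CaYou app, users receive five prompts a day in the first week and three a day in weeks two to four.

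On unmet user needs in digital interventions, the Introduction says that "this can result in high dropout rates, low adherence and engagement, and reduced effectiveness". The Feasibility measures section also plans engagement metrics and reasons for dropout, but attaches no cut-off to them.

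**The concern.** The two arms face different demands over the 4 weeks. The intervention group carries the app and its daily prompts; the waitlist group does not. If people leave because of the app or its assessment load, they leave from one arm, and a pooled percentage averages that arm with one not exposed to the same load.

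The trial is meant to guide a later full-scale trial. Post-assessment retention among app users is a main planning input for that trial, and the between-group ANCOVA needs post data from both arms. A row that rates yellow or green while most app users are missing would give the wrong signal on the point the trial should settle.

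**Working it through.** **Inputs.** From the protocol: 30 per group, N = 60 (Sample size and power calculation); the criterion 2 cut-offs and denominator (Table 3). The allocation ratio is not given in words ("block randomization (blocks of 4 and 6 to minimize predictability in allocation"); 1:1 follows from 30 per group. Assumed: waitlist completion of 80–90%, because the protocol gives none. The lower end equals the planned 20% dropout.

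**The plan's own figure.** The dropout step fits 30 per group: 24 / (1 − 0.20) = 30. Whether 24 follows from the stated effect size and power is a separate matter; only the 30 and the 60 are used here.

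**Pooled rule.** Completeness = (IG completers + WLC completers) / 60, where IG is the intervention group and WLC the waitlist group. Red is avoided from 0.50 × 60 = 30 completers. Green needs more than 0.70 × 60 = 42, so at least 43. The smallest IG count for each colour is therefore 30 − WLC and 43 − WLC.

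| WLC complete | IG needed for yellow | IG needed for green |
|---|---|---|
| 24/30 (80%) | 6/30 (20%) | 19/30 (63%) |
| 27/30 (90%) | 3/30 (10%) | 16/30 (53%) |
| 30/30 (100%) | 0/30 (0%) | 13/30 (43%) |

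Check: (24 + 6)/60 = (27 + 3)/60 = 50.0%; (24 + 19)/60 = (27 + 16)/60 = 71.7%.

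**Smaller sample.** With 45 recruited (23 IG, 22 WLC) and WLC 20/22 (91%), yellow needs 3/23 (13%) and green 12/23 (52%). The pattern does not depend on N = 60.

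**By arm.** With the same cut-offs on 30 people, yellow starts at 0.50 × 30 = 15. Green needs more than 21, so at least 22.

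**Chance of avoiding red**, with independent binomial counts, 30 per arm:

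| True IG | True WLC | Pooled rule | IG alone |
|---|---|---|---|
| 20% | 80% | 0.56 | <0.001 |
| 20% | 90% | 0.90 | <0.001 |
| 30% | 80% | 0.85 | 0.017 |
| 30% | 90% | 0.99 | 0.017 |

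**Price of rating by arm.** Suppose true completion is 80% in both arms. Pooled, the chance of missing green is P(X ≤ 42 of 60) = 0.043. In one arm it is P(X ≤ 21 of 30) = 0.129, so for the worse of two arms it is 1 − (1 − 0.129)² = 0.24. The chance of red is about 0.0001 by arm and smaller still pooled.

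**The case against.** **Other criteria also count.** A reader might infer from the table that a trial with no intervention-group post data could be declared feasible. The documents do not support that. The zero case rates yellow only if all 30 waitlist participants are complete; at 29 of 30 it is 29/60 = 48.3%, red. All seven criteria must also be yellow or green. Without intervention-group post data, criterion 6 (PHQ-4 change against control) could not be rated and criterion 7 would lose the post-assessment INEP-On. This objection stands against the extreme case. It is weaker for partial loss, when criteria 5, 6 and 7 can still be computed on those who remain.

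**Criterion 3 may flag app disengagement.** It scores daily EMA completion, with red below 40%. If only intervention-group EMA counts over 60 people, 13 sustained users give 13/60 = 22%, red; over the intervention group alone they give 13/30 = 43%, yellow. So it would be wrong to say that loss in that arm goes wholly unflagged. But EMA completion is not post-assessment completion, and this row too is worded on the total sample although EMA is collected in the app.

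**Pooling suits a data-collection criterion.** Completeness belongs to the domain on data collection procedures, and the feasibility of a two-arm trial concerns both arms. Adherence and reasons for dropout are recorded elsewhere, and those who discontinue are invited to interview. This is fair, but none of those items carries a cut-off.

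**Better waitlist retention is assumed.** This stands. The protocol does not say that waitlist dropout is lower, and no participant is paid. Nor does it follow that the ANCOVA would be badly biased: that depends on why data are missing and on how missing data are handled, which an analysis plan may specify.

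**Conclusion.** The point holds for criterion 2 as a row. Its stated denominator lets waitlist completers stand in for missing app users. At an assumed waitlist completion of 80–90%, the row stays yellow with 10–20% of the intervention group complete and turns green at 53–63%. This needs no perfect waitlist retention, since it already occurs at the planned 20% dropout. No other traffic-light criterion limits missing post-assessment data in the intervention group.

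The sizes rest on 30 per arm and on the assumed waitlist range. The point concerns what this row can detect, not the overall feasibility verdict. It is a worthwhile, inexpensive improvement rather than a flaw that invalidates the trial.

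**What to change.** Reword criterion 2 so that the existing cut-offs (>70%, 50–70%, <50%) apply to each arm separately and the row takes the rating of the worse arm. With 30 per arm, yellow then starts at 15 completers and green at 22. Report the between-arm difference in completeness with a 95% confidence interval.

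This changes one table row and needs no extra data. The cost is the less stable green rating worked out above, about 24% against 4% for missing green at true 80% completion, with the chance of red still negligible. A yellow rating prompts only discussion and minor adjustments, so that cost is modest.

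The change does not align the row with the planned 20% dropout: 22 of 30 is a 27% loss and would still be green. That gap comes from the 70% threshold and not from pooling.

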##### Data collection time points

3.2.4.1

Assessments will take place at screening (T0), baseline (T1), 10 days post-randomization (T2, only IG), and 4 weeks post-randomization (T3, post-intervention). Data collection includes online self-reports and telephone-based diagnostics (SCID-5). In-app assessments include daily EMA (PHQ-4) and repeated measures every 4 days (PHQ-4, TYDQ, CBTSQ [Things You Do Questionnaire and Cognitive-behavioral Therapy Skills Questionnaire]). In the IG, additional qualitative interviews after the app usage phase take place to explore their experiences with the study process, app usage, its acceptance, as well as facilitators and barriers to its application. Those who have discontinued the intervention will also be invited to identify barriers and reasons for dropout. An overview of all assessments and instruments is provided in Table 2.

**Table 2 tab2:** Assessment overview.

Instrument	Variable	Time of measurement					
		Screening	T0 Baseline	T1 10 Days	T2 Post	Daily	Course 4-days
Self-developed items	Inclusion criteria	x					
PHQ-ADS	Anxiety and depression	x					
BDI-II Item 9	Suicidal thoughts and behaviors	x			x		
PHQ-4	Anxiety and depression		x		x	x	x
Self-developed items	Sociodemographic data		x				
Self-developed items	Current medication		x		x		
ZUF-8	Treatment satisfaction			x	x		
Self-developed items				x	x		
TYDQ	Behaviors that promote mental health		x		x		x
INEP-On	Positive and negative effects of app use				x		
CBTSQ	CBT-Skills		x		x		x
SUS	Usability			x	x		
Self-developed items	Acceptability of data collection procedures				x		
Self-developed items	Concurrent treatment				x		
Self-developed items	Reasons for drop-out			x	x		
Diagnostic interviews							
SCID-5	Mental disorders, comorbidities, severity and chronicity		x				

PHQ-ADS, Patient Health Questionnaire Anxiety and Depression Scale; PHQ-4, Patient Health Questionnaire-4; BDI-2, Beck Depression Inventory-2; ZUF-8, Questionnaire for Patient Satisfaction 8; TYDQ, Things You Do Questionnaire; INEP-On, Inventory for Assessment of Negative Effects of Psychotherapy adapted to Online interventions; CBTSQ, Cognitive-Behavioral Therapy Skills Questionnaire; SUS, System Usability Scale; SCID-5, Structured Clinical Interview for DSM-5.

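### Table 3, criterion 3 takes EMA completion over the total sample although only the intervention arm has the app for the 4 weeks, so the score stops at about 50% and green is out of reach unless later waitlist EMA counts

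*Protocol article*

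**What the plan says.** Section 3.2.4.2 (Feasibility measures), Table 3, sets seven traffic-light criteria. The third is "Completed EMA data (at least one EMA completed per day; percentage of the total sample", with green above 60%, yellow 40–60% and red below 40%. The second criterion, on post-assessment data from both arms, uses the same denominator: "Participants with complete data at post-assessment (percentage of the total sample".

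Four other statements bear on this row:

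- **Where EMA is collected.** Section 3.2.4.1 (Data collection time points): "In-app assessments include daily EMA (PHQ-4) and repeated measures every 4 days". Section 3.2.2 likewise describes the EMA prompts as part of the app.
- **Who has the app.** Section 3.2.1.3 (Randomization): "those in the IG will receive immediate access to the CaYou app, while WLC participants will gain access after 4 weeks".
- **When follow-up ends.** The last time point listed in Section 3.2.4.1 is "4 weeks post-randomization (T3, post-intervention".
- **How the ratings are used.** Section 3.2.5.1 (Quantitative data analysis): "The intervention is considered feasible if all criteria in the traffic light system are rated yellow or green". A red rating points to major revision with outside advice.

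Section 3.2.3 plans 30 participants per group and 60 in total.

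**The concern.** The numerator of criterion 3 can come only from people who hold the app. During the 4 weeks of the comparison that is one arm of two. The denominator, read in its ordinary sense and in line with criterion 2, is everyone randomised. About half of it cannot contribute a single EMA in that period, however well the app and its prompts work.

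The cut-offs are ones that would suit a group in which every member could respond. Applied to a denominator twice that size, they no longer separate good from poor completeness as the three colours intend. Because no criterion may be red, this row alone could decide that the feasibility rule is not met. The alternative would be to change the denominator once the data are in, which undoes the purpose of fixing the criteria in advance.

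**Working it through.** **Inputs**

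- 30 per group, 60 in total (Section 3.2.3).
- Randomisation in blocks of 4 and 6 (Section 3.2.1.3).
- App and EMA available to the IG only, from randomisation to week 4 (Sections 3.2.1.3 and 3.2.4.1).
- Cut-offs of 40% and 60% (Table 3).
- Anticipated dropout of 20% (Section 3.2.3).
- Assumption: waitlist EMA after week 4 is not counted.

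The cut-offs are design choices, so there is no plan figure to reproduce beyond the total, 2 × 30 = 60, which agrees.

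**Step 1: the ceiling.** Let k be the number of IG participants who meet the EMA requirement. As written, score = k/60, which is half of the IG proportion k/30. The maximum is 30/60 = 50%. If the unit is person-days, the maximum is (30 × 28)/(60 × 28) = 840/1,680 = 50%, so the ceiling does not depend on the unit.

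**Step 2: chance imbalance.** With blocks of 4 and 6, an unfinished last block can leave the arms at most 3 apart. For totals from 45 to 60, the most favourable case is N = 45 with 24 in the IG: 24/45 = 53.3%. This is still below 60%.

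**Step 3: the cut-offs expressed as IG completion.**

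- Green needs k/60 > 60%, so k > 36. Only 30 are available.
- Yellow needs k/60 ≥ 40%, so k ≥ 24, which is 24/30 = 80% of the IG.
- Red is k ≤ 23, which is any IG completion below 80%.

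**Step 4: ratings on the two denominators.**

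| IG participants meeting the requirement | Over 30 | Rating | Over 60 | Rating |
|---|---|---|---|---|
| 30 | 100.0% | green | 50.0% | yellow |
| 27 | 90.0% | green | 45.0% | yellow |
| 24 | 80.0% | green | 40.0% | yellow |
| 23 | 76.7% | green | 38.3% | red |
| 19 | 63.3% | green | 31.7% | red |
| 18 | 60.0% | yellow | 30.0% | red |
| 12 | 40.0% | yellow | 20.0% | red |
| 11 | 36.7% | red | 18.3% | red |

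The rating is one or two colours worse as written for every k from 12 to 30. The two denominators agree only at 11 or fewer.

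**Step 5: the plan's own dropout.** 20% of 30 is 6, leaving 24. If all 24 comply, the score is 24/60 = 40.0%, the lowest value that rates yellow. One further non-complier gives 23/60 = 38.3%, which is red.

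**Step 6: if waitlist EMA does count.** If each arm is observed over its own 4 weeks of app access, the maximum becomes 60/60 = 100% and all three colours are reachable. The defect then lies only in the row not saying so.

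**The case against.** The strongest reply is that the ceiling is conditional. Criterion 3 states no time window, waitlist participants eventually receive the same app with EMA built in, and Figure 1, whose legend lists EMA, is not available in the text reviewed. If waitlist app use is included, a total-sample denominator makes sense. This stands as a condition on the finding. Against it, no section states a waitlist EMA window, the last listed assessment is at 4 weeks, and Section 3.2.4.2 measures app usage over the 4-week period. The article also marks IG-only items elsewhere (the 10-day assessment and the interviews) but not here, so reading total sample as a silent reference to the IG has no support either.

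Four stronger readings are tempting, and the article does not carry them:

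- *Good completion always rates red.* It does not: 80–100% IG completion rates yellow, and yellow satisfies the feasibility rule.
- *The row is the plan's test of app adherence.* Section 3.2.4.2 places EMA completeness under data collection. Adherence is measured separately, by modules and exercises completed, usage days and buddy interactions.
- *A red rating ends the programme.* It fails the feasibility rule, but the stated consequence is major revision.
- *Everyone must respond on all 28 days, so nearly all would fail.* With independent days and a 90% daily response, 0.90^28 is about 5%. That needs the harshest reading of the row, and independence is doubtful because EMA response tends to cluster within persons. The row is headed by data rather than participants, so a person-day reading is at least as natural. What remains is that the unit is not named.

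It can also be said that scoring detail belongs in a fuller document. Here, however, the article itself fixes a denominator and cut-offs that do not fit the design. That is a stated rule, not an omission.

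**Conclusion.** Criterion 3 is wrong as written. Its denominator includes an arm that has no access to EMA during the 4-week comparison. Assuming 30 per arm and no credit for waitlist EMA after week 4, the score is capped at 50% (about 53% under the most favourable imbalance and a recruited total of 45). Green cannot be reached, 80–100% IG completion is yellow, and less than 80% is red. The harmful zone is IG completion from 40% to below 80%, which would rate yellow or green over the IG but is red here and so fails the feasibility rule. The finding concerns one row of the feasibility table. It does not touch randomisation or the between-group ANCOVA.

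**What to change.** Before any data are seen, reword this one row of Table 3:

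1. Replace the total-sample denominator with participants randomised to the IG, over the 4-week app period.
2. Keep the cut-offs of above 60%, 40–60% and below 40%.
3. Name the unit. One option is IG person-days with at least one completed EMA, divided by scheduled IG EMA days. If participants are the unit, state what a participant must do to count. With 30 in the IG, 19 or more is then green, 12–18 yellow and 11 or fewer red, so every colour can occur.
4. If waitlist EMA is meant to count, state that instead and score each participant over their own 4-week access window.

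The first route needs no extra data, participants or analysis, only an amended table row and a dated note in the registration. The second also needs waitlist EMA to be retained for the 4 weeks after access, which delays the rating of this criterion by that time.

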#### Study design

3.2.1

In Stage II, a two-arm randomized-controlled proof-of-concept trial will compare the intervention group (IG) using the CaYou app for 4 weeks with a waitlist control group (WLC), who will receive access after 4 weeks. An overview of the Stage II design is shown in Figure 1.

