1) Recruitment capability and resulting sample characteristics: Recruitment capability will be assessed by the number of individuals expressing interest in study participation, the intervention uptake rate, and the time required to reach the target sample. The traffic light system will evaluate whether the planned sample size (*N* = 60) is achieved within the 12-week recruitment period (see Table 3). Sample characteristics will be collected through sociodemographic data (e.g., age, gender, education, employment, relationship and parental status, residence size, nationality, ethnicity, migration status), family history of anxiety or depression, prior diagnoses, psychotherapy history, current medication or treatment, and experience with digital mental health tools.2) Data collection procedures and outcome measures: The appropriateness of data collection will be assessed through EMA and T2 data completeness, psychometric evaluation of outcome measures, and feedback from the study team. Participant perspectives on acceptability and appropriateness will be gathered at T2 using self-developed items and in the qualitative telephone interviews based on a custom interview guide (IG participants only).3) Acceptability and suitability of intervention and study procedures: Acceptability, satisfaction, and usability of the app will be measured using the German version (ZUF-8; *α* = 0.90, 8 items, score range: 8–32) of the Client Satisfaction Questionnaire (CSQ) (71), the System Usability Scale (SUS; *α* = 0.91, 10 items, score range: 0–40) (72), and self-developed items. At T2, qualitative telephone interviews will further explore participants’ experiences with the app’s features, content, and overall impressions. Intervention adherence will be measured via user engagement metrics (e.g., number of modules and exercises completed, usage days during the 4-week period, buddy interactions, and optional sensor data). Reasons for dropout will be assessed through self-developed items and within the qualitative interview at T2.4) Resources and ability to manage and implement the study and intervention: The study team will document time and personnel resources needed for app development, study administration, and participant support.5) Participant responses to the intervention: Symptoms of anxiety and depression will be measured using the Patient Health Questionnaire Anxiety and Depression Scale (PHQ-ADS; *α* = 0.88–0.92, 16 items; score range: 0–48) (73), which combines the Patient Health Questionnaire 9 (PHQ-9; *α* = 0.89, 9 items, score range: 0–27) (51, 74) and the Generalized Anxiety Disorder Scale 7 (GAD-7; *α* = 0.89, 7 items, score range: 0–21) (75). The PHQ-ADS has shown high internal consistency (*α* = 0.88–0.92). Cognitive behavioral skills will be measured using the Cognitive-behavioral Therapy Skills Questionnaire (CBTSQ; *α* = 0.90, 16 items, score range 16–80), covering behavioral activation (*α* = 0.85) and cognitive restructuring (*α* = 0.88) (76). The Things You Do Questionnaire (TYDQ; *α* = 0.90, 15 items, score range: 0–60) (77) will assess engagement in positive routines and meaningful activities, with higher scores indicating greater engagement (*α* = 0.90). Qualitative interviews at T2 will explore the perceived effects of the app from the IG participants’ perspective.6) Risks and negative events: The benefit–risk ratio will be assessed by tracking adverse events, including reliable symptom improvement and deterioration according to the reliable change index (RCI) by Jacobson and Truax for the PHQ-ADS, indicating a decrease or increase of >1.96 from T1 to T3 as well as suicidal thoughts and behaviors (78). These will be measured at T2 using the INEP-On (Inventory for Assessment of Negative Effects of Psychotherapy adapted to online interventions; *α* = 0.86, 21 items) (79), item 9 of the PHQ-ADS (73), and item 9 from the BDI-II (80). Qualitative interviews will further explore perceived negative effects of the app.

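### Table 3, criterion 3 divides EMA completion by both arms although only the intervention arm has the app, so green cannot be reached and the planned 20% dropout alone brings the row to the edge of red

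*Protocol article*

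**What the plan says.** Table 3 in section 3.2.4.2 of the protocol article scores criterion 3 as "Completed EMA data (at least one EMA completed per day; percentage of the total sample", with green above 60%, yellow from 40% to 60% and red below 40%.

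Four other places fix what that percentage can be:

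- Section 3.2.3 sets 30 "participants per group are required, yielding a total sample size of" 60, "accounting for an anticipated 20% dropout rate".
- Section 3.2.1 compares the app group with a "waitlist control group (WLC), who will receive access after 4 weeks". Section 3.2.1.3 repeats this timing.
- Section 3.2.4.1 places EMA inside the app: "In-app assessments include daily EMA (PHQ-4) and repeated measures every 4 days". The last assessment it lists is at 4 weeks after randomisation.
- Section 3.2.5.1 gives the decision rule: "The intervention is considered feasible if all criteria in the traffic light system are rated yellow or green". A red row calls for major rework with outside advice.

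**The concern.** In the four weeks up to the last scheduled assessment, a waitlist participant cannot complete an EMA because he or she does not have the app. Half of the stated denominator is therefore zero by design. The printed cut-offs of 60% and 40% then act as 120% and 80% of the people who can respond.

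The row is decisive, because a single red rating means the feasibility rule is not met. An app whose users complete EMA at a rate well above the printed green mark could be declared not feasible because the control arm lacked access, and not because of how users behaved. Correcting the denominator after the data are seen would weaken a criterion that the protocol presents as predefined.

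**Working it through.** **Inputs**

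- Total sample 60, as 2 × 30 (3.2.3).
- Dropout 20% (3.2.3).
- Bands: green >60%, yellow 40–60%, red <40% (Table 3, row 3).
- Contributors up to week 4: the intervention arm only (3.2.1, 3.2.1.3, 3.2.4.1).

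**What the total sample means.** Row 1 of Table 3 uses N = 60 for both arms, and its percentages reproduce: 45/60 = 75% and 59/60 = 98%. Row 2 uses the same total-sample wording for post-assessment completeness, where both arms do contribute. The denominator of row 3 is therefore 60. Only this number and the dropout rate are used here; the effect-size argument behind 30 per group is a separate matter and plays no part.

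**Ceiling.** If all intervention participants are complete, the result is 30/60 = 50%. Green needs more than 60%: 36/60 is exactly 60%, so at least 37/60 (61.7%) is required. Chance imbalance from the blocks does not help: 31/60 = 51.7%, and with 24 of 45 participants in the intervention arm, 24/45 = 53.3%.

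**Cut-offs expressed per app user.** 0.60 × 60/30 = 120%; 0.40 × 60/30 = 80%.

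**At the plan's own dropout.** 30 × (1 − 0.20) = 24 retained. If all 24 are complete, 24/60 = 40.0%, the lowest yellow value. One fewer gives 23/60 = 38.3%, red.

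**Person-day reading.** If the row is scored as days with at least one EMA, the maximum over four weeks is (30 × 28)/(60 × 28) = 50%. The cap is the same.

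**Chance of each colour.** Let X, the number of EMA-complete intervention participants, be binomial with n = 30 and probability p. The documents give no value for p, so the values below are assumptions. On the total sample, red is X ≤ 23. On the intervention arm, green is X ≥ 19 (19/30 = 63.3%) and red is X ≤ 11.

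| Assumed p | P(red), denominator 60 | P(green), denominator 30 |
|---|---|---|
| 0.70 | 0.840 | 0.841 |
| 0.80 | 0.393 | 0.991 |

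At p = 0.90, P(red) on the denominator of 60 is still 0.026. On the intervention-arm denominator P(red) is below 0.001 at both 0.70 and 0.80.

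**The case against.** The strongest reply is that row 3 states no time window. Everyone in the total sample eventually receives the app, and Table 2 lists EMA under daily and 4-day columns, apart from the visits. If EMA from the waitlist arm's later app phase counts, the ceiling is 100%, and 20% dropout with full compliance gives 48/60 = 80%, green. This is the one reading that removes the cap. It does not rescue the row as written: no section says that later EMA counts, no assessment is scheduled after week 4, and section 3.2.4.2 measures app use over the 4-week period. The design figure is not available to check. Even if this reading was intended, the table would have to say so and give the window.

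A second reply is that yellow still passes, and that red leads to revision and not to stopping. That is true and limits the harm to the feasibility verdict. That verdict is, however, what the study is designed to deliver.

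A third reply concerns how a person is counted as complete. If it means at least one EMA on each of 28 days, then with independent days (an assumption) a daily compliance of 95% gives 0.95^28 = 24% complete, which is red on the intervention-arm denominator too; 97% gives 43%, yellow. This stands as a separate weakness: on that strict reading the daily rule, and not only the denominator, would drive the colour. The total-sample denominator would still halve whatever rate results.

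Finally, the 20% dropout was set for the PHQ-4 sample size and not for EMA adherence. It is used here only as the plan's own figure for loss.

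**Conclusion.** The row is wrong as written. The 50% cap follows from the stated arm sizes and app access, and needs no assumption about user behaviour. Green is unreachable, and yellow requires at least 24 of 30 intervention participants. The planned dropout alone uses up that whole margin. The one condition is that EMA is counted up to the week-4 assessment, which is all that the document schedules.

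The probabilities of red (0.84 at 70% complete, 0.39 at 80%) depend on the assumed rates, on independence between participants and on a per-person definition of completeness; they illustrate the size of the error. Because the row can by itself overturn the feasibility conclusion, it must be corrected before the EMA data are examined.

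**What to change.** In Table 3, row 3, replace the total-sample denominator with *percentage of participants randomised to the intervention group, weeks 1–4*, and keep the 60% and 40% bands. Full compliance then scores 30/30 = 100%, and 20% dropout with full compliance among the rest scores 24/30 = 80%; both are green. Report EMA from the waitlist arm's later app phase separately and leave it out of this row.

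If the sponsor did mean to count waitlist EMA, the table should state this and define the window as each person's own first four weeks of access. That keeps 60 people in the row, but it mixes the randomised period with use after the wait and delays the rating.

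The recommended change costs one phrase and needs no new data or participants. The percentage rests on about 30 people: at 70% the approximate 95% half-width is 1.96 × √(0.7 × 0.3/30) = 0.16. Little is lost, since the other 30 could only have added zeros.
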